## **INCLUSION AND EXCLUSION CRITERIA**

### **3.4.1 Inclusion criteria**

- a. SOCSO insured Malaysian workers who are on medical leave; have not returned to work; and receiving rehabilitation program at PERKESO Rehabilitation Centre.
- b. Wrist fracture involving individual or combined distal radius, distal ulna, distal radioulnar, radiocarpal joint
- c. Extraarticular fracture, partial articular fracture, and/or complete articular fracture

### **3.4.2 Exclusion criteria**

- a. Aged below 18 years old or above 60 years old (based on SOCSO scheme)
- b. Associated peripheral nerve injuries, neuropathy or/and tendon injuries to the affected upper limb
- c. Associated neurological conditions related to the central nervous system
- d. Cognitive impairment or psychiatric condition
- e. Severe and uncontrolled medical conditions e.g. cardiovascular disorders, respiratory disorders, cancer
- f. Cardiac pacemaker
- g. Skin disorders e.g. eczema, psoriasis, open wound etc. of the affected forearm and hand that prevent electrode placements
- h. Severe contracture of the affected wrist joint
- i. Forearm size that is not fit to wear the Single Joint Hybrid Assistive Limb (HAL-SJ) robotic exoskeleton

## **3.5 RESEARCH PROCEDURE**

- a. This research will involve the researcher, Therapist A, Therapist B, Therapist C, the intervention group and the control group.
- b. The researcher is a certified HAL-SJ operator accredited by Cyberdyne Inc. and is competent to conduct the robotic intervention for the intervention group (Appendix A).

- c. Therapist A will be an experienced occupational therapist in the field of hand therapy. She/ He will be given the role as the baseline and outcome assessor as well as conducting the conventional therapy interventions that include ROM exercises, tendon gliding exercise, dexterity exercise, retrograde massage, splinting, progressive functional strengthening, functional activity simulation, work conditioning, and work hardening.
- d. Therapist B will be an experienced physiotherapist who is responsible to conduct the conventional therapy interventions that include heat/cold modalities, therapeutic ultrasound, electrical stimulation, joint mobilization, soft tissue mobilization, and strengthening exercises.
- e. All patients with wrist fracture who are referred to PERKESO Rehabilitation Centre will be categorized through the admission database. Participants will be selected based on the inclusion and exclusion criteria by the Disability Management Department which manages the patient admission procedure. The selected participants will be informed about the study and only be included in the study after giving their informed consent.
- f. The participants will then be randomly assigned to the control and intervention group respectively. Simple randomization with allocation concealment is used to prevent the researcher from influencing which participants are assigned to the intervention group.
- g. An independent Therapist C who is not assessing or treating the participants will be given an equal numbers of random allocation cards with designated alphabet of “C” (Control group) and “I” (Intervention group). Therapist C will then insert each allocation card into an opaque envelope. Each envelope that contains a random allocation card with either “C” or “I” notation will be sealed and enclosed with glue. Therapist C will give the corresponding envelope to each enrolled participant after he/she has completed all the baseline assessment. The selected envelope will be opened by the participant immediately in the presence of Therapist C. Therapist C subsequently records the allocated group of either “C” or “I” for the respective participant on the excel sheet prepared by the researcher. The information regarding participant group allocation will only be known by the researcher and Therapist C. Both the Therapist A and Therapist B will not be informed about the group allocation of each participant.

- h. Both participants from the control and intervention groups will be receiving conventional therapy that includes splinting, scar management, edema management, physical agent modalities, e.g. hot/cold pack, ultrasound, Transcutaneous Electrical Nerve Stimulation (T.E.N.S.), Neuromuscular Electrical Stimulation (N.M.E.S.), passive/active stretching, joint mobilization, strengthening exercises, and hand function training.
- i. Each participant from both the control and intervention groups will receive two conventional therapy sessions daily that include an occupational therapy session and a physiotherapy session on a 5-day/week routine basis. Each occupational therapy and physiotherapy session will last for 90 minutes respectively. In addition to the conventional therapy, the intervention group will receive a 60-minutes HAL-SJ robotic therapy session conducted by the researcher daily on a 5-day/week routine basis within two hours after the conventional therapy sessions.
- j. All participants will be receiving this 5-day/week therapy sessions for a duration of four weeks. Reassessment of therapeutic outcome for both control and intervention groups will be conducted by the Therapist A upon completion of the therapy program after 4 weeks.

### **3.5.1 PROTOCOL FOR CONVENTIONAL THERAPY AND SINGLE JOINT HAL-SJ ROBOTIC INTERVENTION**

| Week | Control Group & Intervention Group
(Conventional Therapy)                                                                                                                                                                                           | Intervention Group
(HAL-SJ Robotic Intervention)                                                                                                                                                                                                                                 |
|------|--------------------------------------------------------------------------------------------------------------------------------------------------------------------------------------------------------------------------------------------------------|-------------------------------------------------------------------------------------------------------------------------------------------------------------------------------------------------------------------------------------------------------------------------------------|
| 1    | 
Interventions to improve joint mobility and to reduce pain:
 
Occupational Therapy:
 
Active and passive range of motion exercise of digits, elbow, and shoulder
 
Active range of motion exercise of wrist and forearm rotation
 | 
HAL-SJ – Gentle Mode
 
i) Extension: 50 repetitions; 3 sets
 
ii) Flexion: 50 repetitions; 3 set
 
iii) Supination: 50 repetitions; 3 sets
 
iv) Pronation: 50 repetitions; 3 sets
 
Parameters:
 
Assist Gain: 75-100
 
Assist Level: x1
 |

|   |                                                                                                                                                                                                                                                |                                                                                                                                                                                                                                                                                                                                                                                                         |
|---|------------------------------------------------------------------------------------------------------------------------------------------------------------------------------------------------------------------------------------------------|---------------------------------------------------------------------------------------------------------------------------------------------------------------------------------------------------------------------------------------------------------------------------------------------------------------------------------------------------------------------------------------------------------|
|   | 
Tendon gliding exercise
 
Dexterity exercise
 
Physiotherapy:
 
Joint mobilization
 
Soft tissue mobilization
 
Retrograde massage
 
Heat/Cold modalities
 
Ultrasound
 
Electrical stimulation
 | 
Flexion/Extension Signal Balance:
 
100%/100%
 
Active/Relax Phase:
 
10 seconds/10 seconds
                                                                                                                                                                                                                                                                                       |
| 2 | 
Interventions to improve joint mobility and pain
 
PLUS
 
Occupational Therapy:
 
Functional activities training
 
Physiotherapy
 
Isometric strengthening exercises
 
Isotonic strengthening exercises
   | 
HAL-SJ – Gentle Mode
 
i) Extension: 50 repetitions; 3 sets
 
ii) Flexion: 50 repetitions; 3 sets
 
iii) Supination: 50 repetitions; 3 sets
 
iv) Pronation: 50 repetitions; 3 sets
 
Parameters:
 
Assist Gain: 50-75
 
Assist Level: x1
 
Flexion/Extension Signal Balance:
 
100% : 100%
 
Active/Relax Phase:
 
10 seconds/10 seconds
 |
| 3 | 
Interventions to improve joint mobility and pain
 
PLUS
 
Occupational Therapy:
 
Functional activities training
 
Physiotherapy:
 
Isometric strengthening exercises
                                          | 
HAL-SJ – Gentle Mode
 
i) Extension: 50 repetitions; 3 sets
 
ii) Flexion: 50 repetitions; 3 sets
 
iii) Supination: 50 repetitions; 3 sets
 
iv) Pronation: 50 repetitions; 3 sets
 
Parameters:
 
Assist Gain: 25-50
 
Assist Level: x1
                                                                                                                     |

|   |                                                                                                                                                                                                                                                                                                                                                               |                                                                                                                                                                                                                                                                                                                                                                       |
|---|---------------------------------------------------------------------------------------------------------------------------------------------------------------------------------------------------------------------------------------------------------------------------------------------------------------------------------------------------------------|-----------------------------------------------------------------------------------------------------------------------------------------------------------------------------------------------------------------------------------------------------------------------------------------------------------------------------------------------------------------------|
|   | Isotonic strengthening exercises
Progressive resisted exercises
Open kinetic chain activities
Closed kinetic chain activities                                                                                                                                                                                                                        | Flexion/Extension Signal Balance:
i) 50% : 100%
ii) 100% : 50%
Active/Relax Phase:
10 seconds/10 seconds                                                                                                                                                                                                                                                  |
| 4 | Interventions to improve joint mobility and pain

PLUS
Occupational Therapy:
Work activity simulation
Work conditioning
Work hardening

Physiotherapy:
Isometric strengthening exercises
Isotonic strengthening exercises
Progressive resisted exercises
Open kinetic chain activities
Closed kinetic chain activities | HAL-SJ – Gentle Mode
i) Extension: 50 repetitions; 3 sets
ii) Flexion: 50 repetitions; 3 sets
iii) Supination: 50 repetitions; 3 sets
iv) Pronation: 50 repetitions; 3 sets

Parameters:
Assist Gain: 0-25
Assist Level: x1
Flexion/Ext Signal Balance:
i) 25% : 100%
ii) 100% : 25%
Active/Relax Phase:
10 seconds/10 seconds |

### 3.6 STUDY INSTRUMENTS

#### 3.6.1 Single Joint Hybrid Assistive Limb (SJ-HAL) Robotic Exoskeleton

Single Joint Hybrid Assistive Limb (HAL-SJ) robotic exoskeleton is certified by ISO 13485:2016 (certificate number: 1757.181211) and EC (registration number: DD 601417310001) for rehabilitation and physical therapy usage. The upper limb HAL-SJ is a wearable movement support robot that detects bioelectrical signals on the skin surface and assists joint movements by controlling and operating an actuator placed outside the respective joint. The power units of HAL generate power assist torque by amplifying the wearer's own joint torque estimated from his/her bioelectrical signals, and the support

motions are consequently controlled. It is a safe device that can be used for rehabilitation intervention as approved by the FDA, EC and MDA. It may cause several minor problems: (a) skin allergy or reddening of area where electrode is affixed, however, the reddening should disappear shortly after the electrode was taken off; (b) abrasion of areas that contact the device e.g. cuffs and straps; and (c) muscle and joint soreness (due to post exercise effect). The researcher of this study, who is a certified HAL-SJ operator accredited by Cyberdyne Inc. will take necessary precaution and careful supervision throughout the entire HAL-SJ robotic exoskeleton session to minimise these problems. The medical and healthcare teams of the facility (PERKESO Rehabilitation Centre) including the doctors, medical assistants, and nurses will be consulted immediately if the problems are serious enough to warrant medical treatment. The HAL-SJ robotic exoskeleton that will be used is shown as Figures 1 and 2.

[figure not shown]

Given outcome measures commonly used for wrist fractures include wrist ROM measurement, grip/pinch strength measurement (with dynamometer and pinch gauge), pain measurement (Visual Analogue Scale), and the Disabilities of the Arm, Shoulder and Hand (DASH) Outcome Measure (Weinstock-Zlotnick & Metha 2016), all these outcome measures will be used in this study. In addition, both Purgue Pegboard Test and Box and Block Test will be used to evaluate the functional performance in term of hand dexterity while the readiness to work will be evaluated by using the LAM Assessment on Stages of Employment Readiness (LASER) Questionnaire.

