studies had proved the safety and feasibility of the upper limb HAL-SJ application for the upper limb rehabilitation of quadriplegia patients (Kubota et al. 2018; Shimizu et al. 2017). The upper limb HAL-SJ is also proven safe and effective to be used for the rehabilitation following traumatic brachial plexus injury (Kubota et al. 2017). A newly developed wrist joint attachment to the HAL-SJ is currently available and is capable of assisting voluntary articulatory movements of the wrist joint including wrist flexion and extension as well as forearm supination and pronation.

Robotic technologies have been developed for motor rehabilitation and such robots have shown favourable results when compared with equivalent doses of usual clinical therapy (Lo et al. 2010; Novak 2018). Compared to manual therapy, robotic intervention for rehabilitation has the potential for a greater impact on impairment due to easy deployment, its applicability across of a wide range of motor impairment, its high measurement reliability, and the capacity to deliver high dosage and high intensity training protocols for a longer duration, irrespective of the skills, and fatigue level of the therapist (Huang & Krakauer 2009). Based on the understanding that the amount and intensity of exercise and the quality of motor learning are positively associated with rehabilitation outcome as aforementioned and the fact that HAL-SJ is a newly developed robotic intervention device that shares similarities on the therapeutic features provided by other robotic devices, the application of the HAL-SJ is hypothesized to provide similar positive outcome for wrist fractures. Investigating the outcome of HAL-SJ among upper limb injured workers, especially those with wrist fractures shall provide further evidence on the effectiveness and feasibility of robotic interventions in the field of hand therapy and upper limb rehabilitation.

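### The protocol names three expected device problems, but no visible form records them and no harm rate can be reported by arm

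*Combined protocol and SAP*

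**What the plan says.** Section 3.6.1 lists three problems that the device may cause. They are "a) skin allergy or reddening of area where electrode is affixed", then "abrasion of areas that contact the device e.g. cuffs and straps", then soreness of muscles and joints after exercise. The researcher is to take precautions and supervise throughout each robot session. The centre's doctors, medical assistants and nurses "will be consulted immediately if the problems are serious enough to warrant medical treatment".

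Section 3.5(g) states that only the researcher and Therapist C know the allocation: "Both the Therapist A and Therapist B will not be informed about the group allocation of each participant". Therapist A is also the baseline and outcome assessor (3.5(c)). Under 3.5(h), both arms receive T.E.N.S., N.M.E.S., splinting and strengthening. Under 3.5(i) and (j), the robot arm adds one session a day, five days a week, for four weeks.

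Appendix J, the clinical data record sheet, has 12 items, all outcome measures taken at an initial assessment and a reassessment. Appendix B collects sociodemographic and injury data. Section 3.8 describes the outcome and background variables and tests each hypothesis by mixed-model ANOVA. It does not mention harms.

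**The concern.** The plan foresees specific problems but provides no means of recording them. What becomes known will depend on one allocation-aware observer in one arm, who has no form to fill in. The control arm has comparable exposures (skin electrodes, splints, strengthening), so reddening and soreness are plausible there too. Without a control-arm count, a finding in the robot arm cannot be set against background.

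This matters more here because the application is new. The Introduction says "A newly developed wrist joint attachment to the HAL-SJ is currently available", and the upper-limb HAL-SJ safety reports it cites concern quadriplegia and brachial plexus injury, not wrist fracture. The trial could report benefit with no harm rate beside it. Harm data not collected during the four weeks cannot be recovered at analysis.

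**Working it through.** **The plan's own figure.** Section 3.3 gives 34 participants, raised to 38 for 10% dropout, from a within-between interaction with f = 0.25, alpha 0.05 and power 80%. With 2 groups and m = 2 time points, and assuming a correlation rho = 0.5 (not stated), the noncentrality is f² x N x m / (1 - rho) = 0.0625 x 34 x 2 / 0.5 = 8.5 on 1 and 32 degrees of freedom. Power is 0.807; N = 32 gives 0.781. So 34 reproduces under that assumption, and both 34 x 1.1 = 37.4 and 34 / 0.9 = 37.8 round up to 38. The figure is not in dispute; it fixes the number available for harms.

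**Where each problem could be recorded.**

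| Problem | Who is assigned to look | Visible form field | Control arm |
|---|---|---|---|
| Skin allergy or reddening | Researcher, robot sessions | None | Electrodes used; nobody assigned |
| Abrasion | Researcher, robot sessions | None | Splints used; nobody assigned |
| Soreness | Researcher, robot sessions | No harm field; overlaps the VAS and DASH pain and stiffness items (24, 25, 28) | Same VAS and DASH items at the same two dates |

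The VAS and DASH give two readings four weeks apart. An episode in week 2 that settles by week 3 leaves no trace, and a high week-4 score cannot be tied to a session or a cause.

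**Exposure without a record.** Equal numbers of allocation cards (3.5(g)) give 19 per arm if all 38 are enrolled and all cards are used. Sessions per participant: 5 x 4 = 20. Scheduled robot sessions: 19 x 20 = 380.

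**What a log could and could not show.**
- Zero events in n participants gives a one-sided 95% upper bound of 1 - 0.05^(1/n): 14.6% for n = 19 and 16.2% for 17 completers. The two-sided 95% exact limit for n = 19 is 1 - 0.025^(1/19) = 17.6%.
- The chance of at least one affected participant among 19 is 1 - (1 - p)^19. For assumed true rates of 5%, 10% and 20% this is 0.62, 0.86 and 0.99.
- Power to compare arms of 19 is about 0.53 for 30% against 5%, and 0.79 for 50% against 10% (assumed rates).

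A log would probably record a problem affecting one participant in ten or more. It would not support a test between arms except for very large differences.

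**The case against.** The strongest reply is that the plan is not silent on safety. It names the likely problems, calls them minor, cites regulatory approvals, requires supervision in every session and provides immediate access to medical staff. Soreness overlaps with pain scores collected in both arms. With 19 per arm, a harms comparison would have little power anyway. Some pages, Appendix K and the flow chart are not visible, so a harm form cannot be excluded absolutely.

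Most of this stands as a limit on the point. An action does exist; what is missing is any grading of when to take it. Pain data do exist, but they are not event data. Low power argues against a test, not against counting. The appendices as the text describes them, A to L, include no harm form.

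Three stronger readings are tempting, and the documents do not support them.
- A reader might infer that a skin lesion that would bar entry may carry on to the next session. Section 3.4.2(g) begins "Skin disorders e.g. eczema, psoriasis, open wound etc", but it is limited to conditions of the affected forearm and hand that stop electrodes being placed. A cuff abrasion away from the electrodes need not meet it, and a lesion that does meet it would itself prevent placement. Section 3.5(j) sets a schedule and does not say to treat through lesions. The text is silent on continuing, and silence is not permission.
- A reader might infer a prior harm rate from the cited HAL-SJ reports. Their titles describe case reports or a case study, but the documents give no denominators for harm.
- A reader might add the two 90-minute conventional sessions together as 180 minutes of daily loading on the wrist. Those sessions also cover the digits, elbow, shoulder, massage and heat or cold, and strengthening starts only in week 2.

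**Conclusion.** The point holds as a gap in data collection and reporting. The problems named in 3.6.1 are watched for in one arm only, by a person who knows the allocation. No visible form has a field for them, and 3.8 plans no summary. Reddening and abrasion cannot be counted in either arm, and soreness cannot be counted, dated or attributed. The extent is 380 scheduled robot sessions without a structured harm record, and no usable harm rate by arm.

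This rests on 38 enrolled, 19 per arm and full attendance, and on the forms that are visible. The plan does not permit treatment through lesions, and it does not lack a medical response. Two narrower gaps remain: the threshold for consulting the medical team is ungraded, and the skin criterion is not stated to apply after entry.

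**What to change.** 1. **Record.** Add to Appendix J a short harm log used identically in both arms: skin reaction, abrasion, soreness, other; with date, action taken and whether a session was missed. The participant completes it and Therapist C, who already knows the allocation and neither treats nor assesses, collects it. Therapist A then does not need to ask about skin marks that could reveal the arm.
2. **Device sheet.** The researcher records events during robot sessions on a separate sheet. Because it exists in one arm only, report it separately; base the by-arm figures on the common log.
3. **Report.** Add to section 3.8 a descriptive table of participants with each event by arm, with exact confidence intervals and no claim of a powered comparison. Note that participants know whether they had the robot, so reporting may differ between arms.
4. **Reconcile.** State in 3.4.2(g), 3.5(j) and 3.6.1 whether the skin criterion applies after entry. The clinical rule is for the study's doctors to set.

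The cost is one form, a few protocol sentences and some paperwork: 38 x 4 = 152 participant entries if weekly, or 38 x 20 = 760 if daily, plus up to 380 researcher entries. Treatment, sample size and endpoints are unchanged. Minor events will become visible in the report.
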